At any time, participants were able to opt out of the PHI and request the deletion of all submitted data without giving reasons. In order to prevent high dropout rates that have been observed in past pedometer-based interventions [13], no bonus will be granted for past achievements if the participant decides to opt out of the PHI.

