### Data Collection and Variables

Data for analysis is partly collected by submission of information by the participants via the Web-based platform of the insurance company and partly by administering a Web-based questionnaire at 2 different points in time (T_1_ and T_2_) over the course of the intervention. After participants registered their pedometer or smartphone at the Web-based platform of the insurance company, the number of steps were synchronized automatically with the Web-based platform each day at midnight. However, participants could choose to deactivate automatic synchronization and enter their step count manually on the Web-based platform. Days where no step data is available (eg, because the pedometer was not worn or not charged) will be treated as missing data. The first measurement (T_1_) is set at the beginning of the PHI for all groups, whereas the second measurement (T_2_) is set at the end of the intervention for the experimental groups and after the first half of the intervention for the control group before they received financial incentives. Additional data, such as age, gender, or participants’ health service billings, were provided by the insurance company. To guarantee appropriate response rates, participants received additional $5 for each time they completed the questionnaire resulting in an additional bonus of $10. See Figure 1 for an overview of the study design.

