### Data Analysis

Due to the nested structure of the data, mixed-effect models will be used for data analysis. As measurements are nested within participants, the step count measurements represent the level 1 unit of analysis, whereas the participants represent the level 2 unit of analysis. A recent article [73] discusses the problem of faking with regard to financial incentives, (eg, faking step counts in order to qualify for financial rewards). This problem applies to our study as step counts could be entered manually. Step count measurements that are unusually high and were manually entered are likely to represent a tendency of faking. Thus, univariate and multivariate outlier analysis [74] will be conducted in order to identify participants that are prone to faking. Changes on outcomes solely measured at T_1_ and T_2_ will be analyzed performing a repeated-measures analysis of variance (rmANOVA). The analyses will be conducted using the nlme-package [75] in R [76] and the typical significance level of α = 5% will be applied.

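### Repeated-measures ANOVA for the two-wave questionnaire outcomes normally uses only people who answered both waves; an all-available-data mixed model would be a cheap and safer choice

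*Protocol article*

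**What the plan says.** The Data Analysis section of the protocol article opens with a general commitment: "Due to the nested structure of the data, mixed-effect models will be used for data analysis". It applies this to step counts nested within participants. It then sets a different method for the questionnaire outcomes: "Changes on outcomes solely measured at T_1_ and T_2_ will be analyzed performing a repeated-measures analysis of variance (rmANOVA". For software it says "The analyses will be conducted using the nlme-package [75] in R [76", and for the test level "the typical significance level of α = 5% will be applied".

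Other sections bear on who will have a T2 answer:

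- **Procedure.** Participants may opt out at any time and have their data deleted. "In order to prevent high dropout rates that have been observed in past pedometer-based interventions", the protocol adds a forfeiture rule: "no bonus will be granted for past achievements if the participant decides to opt out of the PHI".
- **Data Collection and Variables.** "the second measurement (T_2_) is set at the end of the intervention for the experimental groups", but after the first half for controls. Each completed questionnaire earns $5. The one missing-data statement concerns days without step data.
- **Experimental Groups (Textbox 1).** Controls receive no activity reward in months 1 to 3, that is, before their T2.
- **Baseline Characteristics.** Residence and subjective health become covariates for the secondary outcomes. Baseline activity differences are to be handled by group-specific intercepts in mixed-effects models.
- **Strengths and Limitations.** T2 comparisons call for caution because the timing differs by arm. Selective loss before T2 is not mentioned.

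**The concern.** With two waves, the group-by-time test in a classical repeated-measures ANOVA is a one-way ANOVA of T2 minus T1. A person with only one answer contributes nothing to it. Suppose people with low T1 scores are likelier to be lost. The completers then start above the full T1 sample, and regression to the mean makes their average change look too small. If this happens to the same degree in every arm, the error cancels in the between-arm contrast. If it differs by arm, part of it remains as a false arm difference.

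The design gives two reasons why loss could differ between the incentive arms and the control arm: 6 months against 3 months to T2, and a forfeitable activity bonus that can act before T2 only in the incentive arms. At stake are the changes in self-reported activity, walking and health perception.

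The text also pulls two ways. Hours of activity and of walking are questionnaire outcomes. Data Analysis would send them to rmANOVA, while Baseline Characteristics speaks of mixed-effects models for baseline physical activity.

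**Working it through.** **The plan's own figure.** No sample size, power or dropout rate is stated for the T1/T2 outcomes. The only sample-size figure, 15,725 customers, belongs to the participation rate. It is consistent with the stated design effect, 1 + (925 − 1) × 0.01 = 10.24, and with whole clusters, 2 × (7 × 925) + 3 × 925 = 15,725. It does not bear on this point.

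**Inputs from the protocol.** T1 respondents: 626 (EG1), 562 (EG2), 131 (CG). T2 at 6 months (EG1, EG2) and 3 months (CG). Test level 5%, taken as two-sided.

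**Assumptions, none of them in the protocol.** Scores are standardised and bivariate normal with T1–T2 correlation ρ, and there is no true change. The log-odds of dropout rise by 0.5 or 1.0 for each SD lower at T1.

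**Formula.** Under these assumptions E[T2 − T1 | completer] = −(1 − ρ) × E[T1 | completer]. The bias of the contrast is therefore −(1 − ρ) × (difference between arms in completers' mean T1).

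**One case in full.** Take ρ = 0.5, dropout 50% (EG) and 25% (CG), slope 0.5. The simulated completer changes are −0.119 and −0.060. These correspond to completer T1 means of 0.119/0.5 = 0.238 and 0.060/0.5 = 0.120. Contrast: −0.119 − (−0.060) = −0.059 SD.

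**Incentive arm minus control, bias of the completers' contrast (SD):**

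| Dropout EG / CG | Slope | ρ = 0.5 | ρ = 0.7 |
|---|---|---|---|
| 30% / 15% | 0.5 | −0.035 | −0.020 |
| 30% / 15% | 1.0 | −0.062 | −0.036 |
| 50% / 25% | 0.5 | −0.059 | −0.035 |
| 50% / 25% | 1.0 | −0.094 | −0.060 |
| 30% / 30% | 0.5 or 1.0 | about 0 | about 0 |
| unequal | 0 | about 0 | about 0 |

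A likelihood estimate using every T1 answer (T2 regressed on T1 within arm, averaged over all T1 respondents) stays within 0.005 SD of zero throughout.

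**Size against the standard error, EG1 vs CG, ignoring clustering.** SE = √(2(1 − ρ)) × √(1/n₁ + 1/n₂).

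- Smallest bias: n = 438.2 and 111.35, ρ = 0.7. SE = 0.775 × 0.106 = 0.082; 0.020/0.082 = 0.24 SE. False-positive rate P(|Z + 0.24| > 1.96), about 6%.
- Largest bias: n = 313 and 98.25, ρ = 0.5. SE = 1.00 × 0.116 = 0.116; 0.094/0.116 = 0.81 SE. False-positive rate P(|Z + 0.81| > 1.96), about 13%.

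**Loss of precision.** The EG1 vs CG difference detectable with 80% power is 2.80 × √(1/n₁ + 1/n₂) SD of change: 0.27 with no dropout, 0.30 at 30%/15% and 0.32 at 50%/25%.

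**EG1 vs EG2, for illustration only (ρ = 0.6, SE about 0.07 SD).**

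- Response 70% vs 50%, equal slopes of 0.5: bias 0.03 to 0.04 SD, false-positive rate about 8%.
- Response 70% vs 50%, slopes 0.3 vs 0.6: 0.07 SD, about 20%.
- Response 60% in both arms, selection in one arm only (slope 0.6): 0.09 SD, about 26%.
- Response 60% in both arms, equal slopes: about 0.

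In the three biased cases the likelihood estimate has bias of at most 0.002 SD, with an SE 0 to 4% smaller.

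**The case against.** **High dropout is not forecast.** A reader might infer that the plan itself expects heavy loss. It does not say so. It cites dropout in past interventions as the reason for a preventive rule, gives no rate, and pays for each questionnaire. This stands: the risk is recognised and its size is unknown.

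**Complete-case deletion is inferred from the method's name.** No sentence says that one-wave respondents are dropped, and nlme can fit models that keep them. This also stands, but only in part. The section sets rmANOVA apart from the mixed models, and the usual meaning of that label for two waves is a both-waves analysis. If an all-available-data fit was intended, the label should be changed to say so.

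**T1 adjustment would remove the bias.** Adjusting the same completers for their own T1 value brings the bias to about zero in the EG1–EG2 scenarios without a mixed model. Subjective health is already a planned covariate, and the Discussion says that prior activity can be controlled for. However, the concrete statement on baseline activity is group-specific intercepts, which do not adjust for an individual's T1 value.

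**EG1 and EG2 share reward amounts, T2 timing and the forfeiture rule.** A reader might conclude from the larger figures that a false EG1–EG2 difference is likely. Nothing in the protocol supports response rates or selection that differ between these arms. The asymmetry built into the design is incentive arms against control.

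**The unbiasedness of the likelihood estimate is partly built in.** Dropout was simulated to depend only on T1, which is the condition that the method needs. This is correct and belongs among the downsides.

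**Missing-data detail may sit in an analysis plan not shown.** This is accepted, and its absence is not the criticism. The point concerns the method that the article does name.

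**Conclusion.** The point holds as a cheap improvement of low to moderate severity. The named method, in its standard form, rests on people with both questionnaires, and a better one is available in the named package. The bias is conditional: T2 non-response must depend on the T1 value and must do so differently by arm. Under the assumed rates and selection strengths it is about 0.02 to 0.09 SD, which for EG1 vs CG is about 0.24 to 0.81 of a standard error. With like loss across arms, or loss unrelated to T1, it is about zero.

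The documents do not show that loss will be high or selective, or that a false arm difference will occur. The participation rate, on which the protocol puts its main focus, does not depend on T2 and is untouched.

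**What to change.** In Data Analysis, replace the rmANOVA for T1/T2 outcomes by a likelihood-based linear mixed model in nlme, with arm, time, arm by time and an unstructured 2 × 2 covariance, fitted to all available T1 and T2 answers. Include the covariates chosen under Baseline Characteristics, except where subjective health is itself the outcome, since its T1 value is then already in the model. This also brings the two sections into line. Report the T2 response rate by arm. Multiple imputation that uses step-sharing data to predict T2 non-response is an optional sensitivity analysis.

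The cost is a few lines of text and slightly more programming, with no new data. Four limits should be stated:

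- The model relies on missing-at-random.
- It cannot recover answers deleted at opt-out.
- It gains little precision.
- It does not make a 3-month T2 comparable with a 6-month T2, so the existing caution must stay.

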**Figure 1 figure1:**
[figure not shown]
Study design.

## Results

### Survey Participation

In total, 1319 persons participated in the survey at T_1_. Of those, 47.46% (626/1319) belonged to the financial incentives group, 42.61% (562/1319) to the charitable incentives group, and 9.93% (131/1319) to the control group.

### Baseline Characteristics

Table 1 presents the baseline characteristics of all T_1_ survey participants for each of the different EGs. Unfortunately, participants’ service billings with the health insurance company were not yet available at the time of writing. Between-group comparisons are based on one-way ANOVA for continuous variables and on chi-square tests for categorical variables. Due to the large number of participants, even small between-group differences are likely to become statistically significant. Hence, effect sizes are reported for between-group comparisons.

Participants were mostly Swiss (1195/1319, 90.60%), living in a village or on the countryside (836/1319, 63.38%), holding a university degree (597/1319, 45.26%), and were 43-years old on average (M=42.95, SD = 13.11). Slightly more men than women participated in the T_1_ survey (638/1319, 48.14% vs 585/1319, 44.35%). A Fitbit pedometer or the Fitbit app was most often used for tracking physical activity (1116/1319, 84.61%) and more than half of the participants (709/1319, 53.75%) bought a pedometer in order to participate in the PHI.

While baseline characteristics show no meaningful group differences regarding age, gender, education, income, nationality, self-reported physical activity at work and during spare time, walking on the way to work, pedometer brand, prior possession of a pedometer, and participation of a family member or friend, group differences could be observed regarding residence of participants, self-reported physical activity and walking, and subjective health status. Differences regarding residence of participants indicate that matching groups according to population density may not be sufficient to account for residence differences.

Because these baseline characteristics are related to physical activity they are primarily relevant for the analysis of the secondary outcomes of the study. Consequently, residence of participants and subjective health status will be used as covariates in the statistical analyses of the secondary outcomes. Because mixed-effects models will be used for data analysis, group differences regarding baseline physical activity will be directly modelled by allowing different intercepts for the experimental groups.

**Table 1 table1:** Demographics and baseline characteristics.

Charachteristic^a^			Total (*N*=1319)	Financial incentives/ EG1 (*n*=626)	Charitable incentives/ EG2 (*n*=562)	Control group/ CG (*n*=131)	*P*	Effect size^b^

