**Demographic variables**								
	Age		42.95 (13.11)	43.06 (13.25)	42.50 (12.88)	44.37 (13.40)	.36	.002
	Gender (%)						.89	.01
		Female	585 (44.35)	285 (45.53)	244 (43.42)	56 (42.75)		
		Male	635 (48.14)	301 (48.08)	270 (48.04)	64 (48.85)		
		Not declared	99 (7.51)	40 (6.39)	48 (8.54)	11 (8.40)		
	Education^d^ (%)						.17	.10
		University	597 (45.26)	301 (48.08)	244 (43.42)	51 (39.69)		
		Professional School	421 (31.92)	194 (30.99)	188 (33.45)	39 (29.77)		
		High School	219 (16.60)	95 (15.18)	95 (16.90)	29 (22.14)		
		Secondary School	25 (1.90)	13 (2.08)	10 (1.78)	2 (1.53)		
		Primary School	6 (0.45)	4 (0.64)	1 (0.18)	1 (0.76)		
		Not declared	51 (3.87)	19 (3.04)	24 (4.27)	8 (6.11)		
	Place of Residence (%)						< .001	.27
		Town	156 (11.83)	92 (14.70)	49 (8.72)	15 (11.45)		
		Outskirts of town	327 (24.79)	185 (29.55)	116 (20.64)	26 (19.85)		
		Village	644 (48.82)	270 (43.13)	303 (53.91)	71 (54.20)		
		Countryside	192 (14.56)	79 (12.62)	94 (16.73)	19 (14.50)		
	Income in CHF (%)						.25	.11
		< 2500	68 (5.16)	29 (4.63)	35 (6.23)	4 (3.05)		
		2501–5000	203 (15.39)	90 (14.38)	91 (16.19)	22 (16.79)		
		5001–7500	418 (31.69)	204 (32.59)	176 (31.32)	38 (29.01)		
		7501–10,000	220 (16.68)	107 (17.09)	87 (15.48)	26 (19.85)		
		>10,000	137 (10.39)	78 (12.46)	50 (8.90)	9 (6.87)		
		Not declared	273 (20.70)	118 (18.85)	123 (21.89)	32 (24.43)		
	Nationality (%)						.03	.13
		Swiss	1195 (90.60)	554 (88.50)	520 (92.53)	121 (92.37)		
		German	56 (4.25)	36 (5.75)	17 (3.02)	3 (2.29)		
		Other	54 (4.09)	32 (5.11)	16 (2.85)	6 (4.58)		
		Not declared	14 (1.06)	4 (0.64)	9 (1.60)	1 (0.76)		

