**Physical activity measures**								
	Self-reported moderate to vigorous physical activity^e^ (hours/week)						< .001	.03
		Mean (SD)	8.90 (11.10)	8.96 (11.38)	8.75 (10.59)	9.26 (11.25)		
		Median	6.00	6.00	6.00	5.25		
	Self-reported walking^e^ (hours/week)						<.001	.03
		Mean (SD)	10.01 (13.70)	10.31 (13.44)	9.99 (15.55)	8.61 (10.87)		
		Median	6.00	6.54	6.00	4.50		
	Physical activity at work		3.45 (1.88)	3.37 (1.84)	3.48 (1.91)	3.67 (1.90)	< .001	.009
	Physical activity during spare time		5.26 (1.17)	5.36 (1.19)	5.19 (1.13)	5.09 (1.22)	.06	.003
	Walking on way to work (%)							
		Yes	234 (17.74)	126 (20.13)	87 (15.48)	21 (16.03)	.10	.06
		No	1085 (82.26)	500 (79.87)	475 (84.52)	110 (84.97)		

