**Other**								
	Subjective health status		3.60 (0.73)	3.66 (0.73)	3.55 (0.71)	3.53 (0.80)	<.001	.02
	Pedometer brand (%)						.73	.09
		Fitbit	832 (62.08)	387 (61.82)	359 (63.88)	86 (65.65)		
		Fitbit App	284 (21.53)	141 (22.52)	121 (21.53)	22 (16.79)		
		Garmin	138 (10.46)	69 (11.02)	55 (9.79)	14 (10.69)		
		Jawbone	65 (4.93)	29 (4.63)	27 (4.80)	9 (6.87)		
	Pedometer bought for participation (%)						.04	.07
		Yes	709 (53.75)	316 (50.48)	325 (57.83)	68 (51.91)		
		No	571 (43.29)	289 (46.17)	221 (39.32)	61 (46.56)		
		Not declared	39 (2.96)	21 (3.35)	16 (2.85)	2 (1.53)		
	Participation of family member or friend						.65	.03
		Yes	251 (19.03)	122 (19.49)	108 (19.22)	21 (16.03)		
		No	1068 (80.97)	504 (80.51)	454 (80.78)	110 (83.97)		

^a^ Unless otherwise indicated, mean (SD) are displayed for continuous variables and absolute frequencies (relative frequencies) are displayed for categorical variables.

^b^ η^2^ is used as a measurement of effect size for one-way ANOVAs and Cramer’s *V* is used as a measurement of effect size for chi-square test. Effect size conventions for η^2^ are: .01 (small effect), .09 (medium effect), .25 (large effect). Effect size conventions for Cramver’s *V* are: .10 (small effect), .30 (medium effect), .50 (large effect) for *df*=1 and .07 (small effect), .21 (medium effect), .35 (large effect) for *df*=2 [77].

^c^ Based on information of the Swiss Federal Office for Statistics for the year 2013 [78].

^d^Categories with expected frequencies <5 were not considered for between-group comparison.

^e^ Due to violation of normality a logarithmic transformation was applied for between-group comparison and the median is reported in addition to the mean.

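### Several Table 1 effect sizes and P values do not reproduce from the table's own data, and the reason given for adjusting for subjective health but not spare-time activity then fails

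*Protocol article*

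**What the plan says.** Under Baseline Characteristics the article states its tests: "Between-group comparisons are based on one-way ANOVA for continuous variables and on chi-square tests for categorical variables". It warns that in a sample of this size small differences will reach significance, and continues: "Hence, effect sizes are reported for between-group comparisons".

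It then sorts the variables. Age, gender, education, income, nationality, activity at work, activity in spare time, pedometer brand and others are said to show no meaningful difference. Residence, self-reported activity and walking, and subjective health are said to differ. The article adds that the latter are related to physical activity, and decides: "Consequently, residence of participants and subjective health status will be used as covariates in the statistical analyses of the secondary outcomes". Baseline physical activity is to be handled by separate intercepts for the groups.

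Table 1 prints, for residence, "Place of Residence (%) < .001 .27". For the row "Subjective health status" it prints P <.001 and eta-squared .02. For activity at work it prints P <.001 and .009, and for "Physical activity during spare time" P .06 and .003. Its footnote sets the scales: eta-squared .01 small and .09 medium; Cramer's V .07 small and .21 medium for df 2.

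**The concern.** An analysis decision is drawn from these effect sizes. Activity at work was called not meaningful although its printed P is <.001, so the effect size evidently carried the judgement. If the effect sizes are wrong, the line between variables that matter and variables that do not is drawn in the wrong place.

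At stake is the stated basis for adjusting the secondary outcomes, chiefly steps and continued use. A measure of a participant's own prior activity, in spare time, was set aside on a figure that the table's data contradict.

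**Working it through.** **Inputs.** Arm sizes from Survey Participation: "47.46% (626/1319) belonged to the financial incentives group, 42.61% (562/1319) to the charitable incentives group, and 9.93% (131/1319) to the control group". Counts, means and SDs from Table 1. Item-level numbers are not printed for the ANOVA rows, so 626, 562 and 131 are assumed. The weighted means this gives (health 3.60, work 3.45, spare time 5.26) equal the printed totals.

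**Rows that reproduce.** The same formulas return the printed values for gender (P .89, V .01), walking to work (.10, .06), pedometer bought (.04, .07) and participation of family or friend (.65, .03). For age they return eta-squared .002 as printed, with P .33 against .36. The method is therefore the article's own.

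**Categorical rows.** V = sqrt(chi² / (N × min(r−1, c−1))).

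Residence counts (financial / charitable / control): town 92/49/15, outskirts 185/116/26, village 270/303/71, countryside 79/94/19. Contributions to chi² by row: 8.96 + 10.92 + 7.91 + 3.43 = 31.23 after rounding, df 6, P about .00002. Hence V = sqrt(31.23 / (1319 × 2)) = .109. A V of .27 would need chi² = .27² × 1319 × 2 = 192.

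The printed value is recovered by multiplying by (rows−1) instead of dividing by min(r−1, c−1): sqrt(3 × 31.23 / 1319) = .267. The same slip accounts for three more rows:

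| Row | chi² | N | Correct V | Value with the slip | Printed |
|---|---|---|---|---|---|
| Residence | 31.23 | 1319 | .109 | .267 | .27 |
| Education (3 largest categories) | 6.40 | 1237 | .051 | .102 | .10 |
| Nationality | 10.84 | 1305 | .064 | .129 | .13 |
| Pedometer brand | 3.57 | 1319 | .037 | .090 | .09 |
| Income | 10.25 | 1046 | .070 | .198 | .11 |

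Income is also wrong, but not by this route. In education, the printed control count of 51 with a university degree conflicts with its own 39.69% and with the row total of 597 (301 + 244 + 52 = 597), so 52 was used. With 51, chi² is 6.64 and V .052. The P values of all five rows do reproduce.

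**Continuous rows.** Eta² = SSB / (SSB + SSW), with SSB = Σ n(mean − grand mean)² and SSW = Σ (n−1)SD². F = (SSB/2) / (SSW/1316).

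| Row | SSB | SSW | F | P | Eta² | Range from rounding | Printed |
|---|---|---|---|---|---|---|---|
| Subjective health | 4.30 | 699.06 | 4.05 | .018 | .0061 | .0050–.0073 | .02, P <.001 |
| Activity at work | 10.84 | 4631.88 | 1.54 | .21 | .0023 | .0021–.0026 | .009, P <.001 |
| Spare-time activity | 12.80 | 1794.90 | 4.69 | .009 | .0071 | .0064–.0078 | .003, P .06 |

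The range moves every mean and SD by up to .005, and none reaches its printed value. For health, P stays between .008 and .036 over that range.

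Two printed pairs also conflict internally. With three groups and N = 1319, eta² .009 gives F = (.009/2)/(.991/1316) = 5.98, P about .003, not <.001. Eta² .003 gives F = 1.98, P about .14, not .06.

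The self-reported walking and moderate-to-vigorous rows were tested on a log scale and cannot be checked from the raw summaries.

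**The case against.** A reader might infer that the adjustment set is itself wrong. The document does not support that. Residence keeps P <.001, exceeds the small threshold of .07 and has the largest V in the table, so it would still be chosen. Adjusting for subjective health is sound even if the arms hardly differ on it.

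It would also be too much to say that spare-time activity clearly differs more than health. The values are .0071 and .0061, their rounding ranges overlap, and both lie below .01. Calling spare-time activity not meaningfully different remains defensible on the corrected value. It is the claim that health does differ that loses support.

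Nor does the article choose on imbalance alone. It gives relation to physical activity as a second reason. The Abstract names baseline physical activity as a covariate, Data Collection and Variables lists age, gender and others as control variables, and Strengths and Limitations says that prior activity can be controlled for. All of this stands and limits the point. But relation to physical activity applies at least as strongly to spare-time activity, so it cannot explain the different treatment.

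Two further inferences should be left aside. The work and spare-time rows might look exchanged, but swapping them does not reproduce either row. One might also fault the baseline tests for ignoring canton, but the article uses them descriptively and plays down significance, and nothing in the calculation here turns on it.

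Missing items could alter the ANOVA rows somewhat. Eta-squared depends mainly on means, SDs and arm proportions, so moderate missingness would not explain a threefold gap for health.

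**Conclusion.** The point holds as a correction of figures and of the reasoning that rests on them. Five categorical effect sizes are too large, four of them through one identifiable slip. Three continuous rows have wrong effect sizes and P values. Residence falls from above medium to small on the table's own scale. Subjective health falls below small and becomes practically equal to spare-time activity, so the contrast that selects one and dismisses the other is not supported.

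The conclusion assumes that the printed counts, means and SDs are right and that the ANOVA rows use close to the full arm sizes. It concerns the secondary outcomes only. The primary outcome, participation rate, does not depend on these entries.

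**What to change.** Recompute the Table 1 effect sizes and P values, and correct the education count or its percentage. Amend the text that sorts variables into meaningful and not meaningful to match.

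Replace the covariate sentence with one that rests on expected relation to physical activity rather than on observed imbalance. Keep residence and subjective health. Add the individual T1 measures already collected (walking, moderate-to-vigorous hours, spare-time activity) with age and gender. This agrees with the Abstract, the list of control variables, and Strengths and Limitations. Group intercepts alone are not a substitute, because they absorb differences in arm means and do not adjust for an individual's own baseline activity. Where a T1 measure belongs to the outcome analysed by rmANOVA, it need not be entered again.

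The cost is table corrections, one sentence and a few model degrees of freedom. No new data are needed.

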**Results:**

Baseline characteristics indicate that residence of participants, baseline physical activity, and subjective health should be used as covariates in the statistical analysis of the secondary outcomes of the study.

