The following variables were measured for analysis: the participation rate represents the primary outcome and is measured by calculating the participation rate in total and for the different groups, respectively. Participation rate is defined as the proportion of active participants that is participants that shared their data with the Web-based platform of the insurance company at least once. Secondary outcomes are continued use of the pedometer, performance of the participants, and health condition. The number of days at which participants share their step count with their health insurance company is used as an indicator of the continued use of the pedometer. The number of steps and the amount of money saved or donated indicate the performance of the participants. Apart from the number of steps, physical activity was also assessed by questionnaire measures namely hours of moderate to vigorous physical activity and hours of walking per week at T_1_ and T_2_ (based on the International Physical Activity Questionnaire [65,66]), walking on the way to work, physical activity at work, and during spare time at T_1_ and T_2_. The proportion of money saved versus donated (at T_1_ and T_2_) is further used to evaluate the charitable incentive condition. We use health perception at T_1_ and T_2_ (“How would you rate your overall health status?”) [67-69] and improvement of health perception due to the intervention at T_2_ (eg, “In general, my health improved due to the prevention program”) [67-69] as subjective measures and service billing with the health insurance company (ie, amount of money repaid by the insurance company per participant) after completion of the prevention program and 1 year later as objective measures in order to assess effects on participants’ health condition. Unless otherwise indicated, a 7-point Likert scale, from strongly disagree (1) to strongly agree (7), will be used for items requiring a response scale.

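### For the health-perception outcome, T1 subjective health is both a response in the rmANOVA and a covariate; as a main effect it cannot adjust the change contrast

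*Protocol article*

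**What the plan says.** Three statements in the protocol article have to be read together.

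- **Outcome.** Methods, Data Collection and Variables: "Secondary outcomes are continued use of the pedometer, performance of the participants, and health condition". Health condition is measured in part by a self-rating of overall health on two occasions: "We use health perception at T_1_ and T_2".
- **Method.** Methods, Data Analysis: "Changes on outcomes solely measured at T_1_ and T_2_ will be analyzed performing a repeated-measures analysis of variance (rmANOVA". The software named is the nlme package in R.
- **Covariates.** Results, Baseline Characteristics: "residence of participants and subjective health status will be used as covariates in the statistical analyses of the secondary outcomes". The reason given is that the groups differed on these variables at T1. The Results part of the abstract has a similar rule: "residence of participants, baseline physical activity, and subjective health should be used as covariates in the statistical analysis of the secondary outcomes of the study".

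No section exempts the health-perception outcome from the covariate rule, and none says whether a covariate enters as a main effect or together with its interaction with time.

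**The concern.** The T1 health rating is one of the two repeated responses when health perception is analysed. The covariate rule puts the same number on the other side of the equation. A covariate that takes one value per person at both occasions has no bearing on a within-person change unless its effect may differ between T1 and T2. The authors would then report a covariate-adjusted group comparison of change whose estimate is the unadjusted one, and whose standard error may be wrong. The cancelling also applies to residence and health as main effects in the other outcomes measured only at T1 and T2, such as the activity questionnaires. The double use does not.

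**Working it through.** **Inputs from the documents.** Table 1: T1 subjective health, mean (SD), is 3.66 (0.73) in the financial arm (n = 626), 3.55 (0.71) in the charitable arm (n = 562) and 3.53 (0.80) in the control arm (n = 131). Data Analysis: 5% level, taken here as two-sided.

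**Assumptions.** The T1–T2 correlation ρ is not given; 0.4, 0.6 and 0.8 are used. The SD is taken as equal at both occasions, every participant has both measurements, and canton clustering is ignored. That the Table 1 item is the T1 health-perception rating is inferred from the wording; no other baseline health rating is described. The plan has no figure of its own to reproduce here.

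**Step 1: cancelling.** With group G, time t (0 or 1), covariate X and person effect u:

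Y = β0 + β1·G + β2·t + β3·G·t + γ·X + u + e

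Y(T2) − Y(T1) = β2 + β3·G + e(T2) − e(T1)

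The term γ·X disappears, whether X is T1 health or residence, so the estimate of β3 is the plain difference in mean change. In one simulated data set (626 against 131, SD 0.73, ρ = 0.6, assumed T2 effect 0.15, T1 difference 0.13) the group-by-time estimate was 0.0774 without T1 health and 0.0774 with it.

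**Step 2: standard error when X is the T1 response.** Write σ² for the within-group variance. With one slope for both occasions, least squares gives γ = (1 + ρ)/2. The residual variances are then:

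- at T1: σ²(1 − ρ)²/4
- at T2: σ²[(1 − ρ)²/4 + 1 − ρ²]
- their average: σ²(1 − ρ)(3 + ρ)/4

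The residual covariance is −σ²(1 − ρ)²/4. It is negative, so a random-intercept variance is forced to 0 and the model treats the two rows as independent. It takes the variance of a person's change as 2σ²(1 − ρ)(3 + ρ)/4, whereas it is 2σ²(1 − ρ). The nominal standard error is too small by the factor √((3 + ρ)/4), and the true type I error is 2[1 − Φ(1.96·√((3 + ρ)/4))].

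In the same data set the fitted standard error fell from 0.0630 to 0.0591 and the random-intercept variance went to 0.

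**Step 3: what the adjustment would have done.** The change contrast is the T2 difference minus the T1 difference. The baseline-adjusted contrast is the T2 difference minus ρ times the T1 difference. They differ by (1 − ρ) × T1 difference. The T1 differences are 3.66 − 3.55 = 0.11 (financial against charitable) and 3.66 − 3.53 = 0.13 (financial against control).

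| ρ | SE ratio | True type I error | (1 − ρ) × 0.11 | (1 − ρ) × 0.13 |
|---|---|---|---|---|
| 0.4 | 0.922 | 7.1% | 0.066 | 0.078 |
| 0.6 | 0.949 | 6.3% | 0.044 | 0.052 |
| 0.8 | 0.975 | 5.6% | 0.022 | 0.026 |

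Over 1000 simulated data sets at ρ = 0.6 with the 0.13 difference, the change contrast averaged 0.098 and the baseline-adjusted contrast 0.150, a gap of 0.052 as in the table.

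**Step 4: with a covariate-by-time term.** Adding T1 health × time in the Step 1 data set gave 0.1464 (SE 0.0550), the same as regressing T2 health on arm and T1 health.

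**The case against.** The strongest reply is that the article never says the covariate enters as a main effect only. With a covariate-by-time term the planned model gives exactly the baseline-adjusted answer, and such detail is often left to a fuller plan. This stands as a limit on the claim: the cancelling depends on coding that is not written down. It does not remove the point, because the article itself fixes the covariate for an outcome of which it is already half, and the plain reading does not deliver the adjustment it announces. The standard-error error is narrower still. It arises in a random-intercept fit, which the named package makes likely; a classical rmANOVA with separate error strata would leave the change test untouched.

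A second reply is that the covariate rule is motivated by relevance to physical activity and was perhaps not meant for health perception. That may be so, but the sentence covers the secondary outcomes without exception.

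A third reply is that baseline adjustment is not plainly better than change scores here. Arms were allocated by canton and the T1 respondents chose to take part: 626/7487 = 8.4%, 562/8216 = 6.8% and 131/2935 = 4.5% of those contacted. If the T1 gap is a lasting group difference, the change contrast is unbiased and the baseline-adjusted one is off by (1 − ρ) × gap. This stands, and it is why the fix includes a sensitivity analysis.

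**Conclusion.** The point holds for one outcome and one mechanism. In the rmANOVA of health perception, T1 health is both response and covariate. As a main effect it leaves the group-by-time estimate unchanged, so it cannot address the imbalance it was chosen for. In a random-intercept model it also raises the true type I error to about 5.6% to 7.1%, for assumed correlations of 0.8 to 0.4. In the other T1/T2 rmANOVAs, residence and health as main effects leave the estimate unchanged too, without that distortion of the standard error.

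Four stronger readings are tempting and are not supported.

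- **That the adjustment halves the group effect.** The group main effect is half the baseline-adjusted T2 difference (0.0732 against 0.1464 in the Step 1 data set) because it averages T1 and T2. Its standard error is halved as well (0.0275 against 0.0550), so t = 2.66 and p = .008 in both. The plan is also about change, not this average.
- **That the change test falsely rejects 17% to 26% of the time because of this error.** Such rates follow for correlations of 0.7 to 0.5 if the 0.11 gap is assumed to regress to a common mean, but they arise with no covariate at all. Under a lasting gap the position reverses, and the baseline-adjusted test would falsely reject about 20% to 33% of the time. This is the general choice between change scores and baseline adjustment.
- **That the same double use applies to baseline physical activity.** The abstract lists it as a covariate, but Baseline Characteristics says those differences are modelled through group-specific intercepts.
- **That all secondary outcomes are affected.** For step counts, days of use and billing, T1 health is an ordinary baseline covariate. The primary outcome, the participation rate, is untouched.

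**What to change.** 1. State that T1 subjective health is not a covariate in the rmANOVA of health perception.
2. If baseline adjustment is wanted, as Baseline Characteristics intends, regress T2 health on arm, T1 health and residence. Equivalently, keep the two-occasion model and give both covariates an interaction with time.
3. In the other T1/T2 rmANOVAs, enter residence and T1 health through their interaction with time.
4. Report the unadjusted change contrast as a sensitivity analysis, since baseline adjustment assumes that the T1 gap is not a lasting group difference.

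The cost is a few sentences and one model line, with no new data. The downside is the reliance on the assumption in item 4. If there is no T1 gap, baseline adjustment gains some precision: in the simulation at ρ = 0.6 (626 against 131, effect 0.15) the standard error was 0.056 against 0.063 and power 74% against 64%. That illustration ignores the different T2 timing in the control arm, a separate limitation that the Discussion already acknowledges.
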